**Methods and analysis:**

We will analyse publicly available quarterly vaccine uptake data (between April 2019 and March 2025) from the Cover of Vaccination Evaluated Rapidly programme for general practices (GPs) in England. The intervention group will be defined as practices located within a 1 km radius of the intervention sites. A synthetic control group will be constructed using non-intervention GPs matched on pre-intervention vaccine uptake, and linked demographic, socioeconomic and healthcare capacity covariates. Primary outcomes are the uptake of MMR1 and MMR2 vaccines. Secondary outcomes include the uptake of 6-in-1, PCV and rotavirus vaccines. Average treatment effects will be estimated as the post-intervention difference in uptake between intervention and synthetic control groups. Sensitivity analyses will examine spillover effects, alternative spatial definitions of exposure, the biasing effect of concurrent interventions and the feasibility of analysis at small area neighbourhood level.

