## Methods and analysis

### Data sources and measures

#### Vaccine uptake

This study will use publicly available data from the Cover of Vaccination Evaluated Rapidly (COVER) programme,^29^ which provides quarterly statistics on the uptake of routine childhood immunisations for children aged 5 years and under at the general practice (GP) level in England.

Our primary outcome is the uptake of the first and second doses of MMR vaccine (MMR1 and MMR2). We will further examine the 6-in-1 vaccine, PCV booster dose and rotavirus vaccine as secondary outcomes, as they are administered at similar ages and often coincide with MMR. Table 1 provides information on the age at which each vaccine is administered, based on the UK childhood vaccination schedule,^30^ and its corresponding COVER reporting age.

**Table 1 T1:** Childhood vaccines included in the analysis, with their recommended administration ages and corresponding measurement points in the COVER dataset

Vaccine	Age administered	Age measured in COVER
DTaP/IPV/Hib/ HepB (6-in-1)	8, 12, 16 weeks	12 months
Rotavirus	8, 12 weeks	12 months
PCV booster	13 months	2 years
MMR1	13 months	2 years, 5 years
MMR2	3 years 4 months	5 years

COVER, Cover of Vaccination Evaluated Rapidly; DTaP, diphtheria, tetanus, pertussis; HepB, hepatitis B; Hib, haemophilus influenzae type B; IPV, inactivated polio vaccine; MenC, meningococcal group C; MMR, measles, mumps and rubella; PCV, pneumococcal conjugate vaccine.

COVER reports vaccine uptake as the percentage of eligible children who received the vaccine by a certain age within a given quarter. A key strength of this dataset is its completeness, with a near universal coverage across the GP-registered child population in England. We will use data spanning 24 consecutive quarters, from April 2019 (the earliest quarter with GP-level data) to March 2025, labelled sequentially from Quarter 1 (Q1) to Quarter 24 (Q24).

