### Covariates

To account for factors that may influence the uptake of the childhood vaccines, we will incorporate a set of covariates that reflect the demographic, socioeconomic context and health-seeking behaviour of the GP-registered population, as well as a range of structural and financial characteristics of the practices. Covariates were chosen based on their theoretical relevance and supporting evidence from existing literature.

The number of children aged 0–4 years and the proportion of males will be included to account for differences in the size and sex structure of the child population in each practice. Socioeconomic deprivation^14 15^ and ethnicity^16^ have been consistently associated with lower immunisation coverage in the UK, possibly due to language barriers, misinformation and mistrust in health services.^31^ We will therefore include the 2019 Index of Multiple Deprivation (IMD) and the proportion of black, Asian and mixed ethnicity as reported in the 2021 census.

Healthcare capacity and quality are also critical, as they directly influence the accessibility and delivery of preventive services.^31^ We will use the percentage of Quality and Outcomes Framework achieved, clinical workforce per 10 000 patients, total funding per patient and average number of appointments per registered patient as proxies for institutional capacity and service availability. The proportion of patient-reported satisfaction with GP services and the proportion of those with caring responsibilities will also be included. These measures capture broader aspects of patient engagement^32^ and competing priorities,^33^ which can shape parents’ ability or willingness to access routine immunisation services and serve as an indirect proxy for service quality.

Lastly, the geographical accessibility of the practices will be proxied using the average distance patients live from their GP. Using the Lower Super Output Area (LSOA)-registered patient population (LSOAs are small statistical areas representing neighbourhoods of ~ 1500 people), we will calculate the straight-line distance from each LSOA centroid to the GP’s physical location. A weighted average of these distances will be applied to each GP based on the number of registered patients for each LSOA. Where feasible, we will explore replacing the straight-line distances with road-based travel times.

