**Figure 2 F2:**
[figure not shown]
Coverage of MMR1 at 2 years and MMR2 at 5 years across Liverpool by MSOA in the year preceding the intervention (April 2022 to March 2023). Red dots with green circles represent the locations of intervention events with a 1 km surrounding buffer, and cyan dots represent the population-weighted centroid of intervention GPs. Coverage data are based on GP-level uptake reported through the COVER programme. COVER, Cover of Vaccination Evaluated Rapidly; GP, general practice; MMR, measles, mumps and rubella; MSOA, Middle Layer Super Output Area.

The pre-intervention period spans Q1 to Q18 (April 2019 to September 2023), with Q19 to Q24 (October 2023 to March 2025) defining the post-intervention period. The average treatment effect will be estimated as the average difference in vaccine uptake between the intervention and synthetic control groups in the post-intervention period.

The statistical significance of estimated effects will be assessed using the permutation inference, following the method described by Robbins and Davenport.^39^ We will perform 250 permutations, reassigning treatment status to control units to generate a distribution of treatment effects under the null hypothesis (ie, no difference in vaccine uptake between the intervention and control groups). All analyses will be conducted using R V.4.4.2 and the microsynth package.^39^

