### Sensitivity analysis

Given the community-based nature of the intervention, there is potential for spillover effects beyond the identified intervention practices. To mitigate this effect, we will conduct a sensitivity analysis excluding other non-intervention GPs located within the central and north Liverpool PCNs from the donor pool practices used to construct the synthetic control group. We will also incorporate a one-quarter lag at the start of the post-intervention period (ie, starts at Q20 instead of Q19) to allow sufficient time for any changes in vaccine uptake to become observable.

To assess the sensitivity of the estimated effect to the exposure’s spatial definition, we will test alternative buffer distances (0.5 km, 1.5 km and 2 km) from intervention event sites. We will further attempt to exclude practices that may have been affected by other concurrent vaccine-related initiatives implemented elsewhere in England. To identify such initiatives, an audit of interventions form will be distributed to immunisation leads at the UK Health Security Agency and to public health leads across the nine local authorities in Cheshire and Merseyside via the Champs Public Health Collaborative. A copy of the form is provided in online supplemental material 1.

Further sensitivity analyses will involve adjusting the pre-intervention period to begin after the final phase of national COVID-19 restrictions in England (February 2022 to Q12 in our dataset), as it could bias the counterfactual estimation. For example, tiered restrictions during the pandemic varied in stringency across England. This has led to regional variation in childhood vaccine uptake^40^ and will consequently affect the SCM matching.

In addition, we will rerun the evaluation using vaccine uptake aggregated to a small area neighbourhood level (LSOA), which may better reflect the community-based nature of the intervention. Finally, to test the robustness of our findings, we will explore alternative approaches to constructing synthetic controls. These may include methods that incorporate negative control series or rely on different assumptions about the counterfactual.

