### Timeline

The study uses data from the COVER programme, with data acquisition limited to downloading and curating publicly released datasets. The audit form is planned for January to April 2026. Data analysis will begin following completion of the audit, and the study is expected to conclude by January 2027.

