### Limitations

First, although we will attempt to account for confounding during the construction of the SCM, bias due to unobserved characteristics remains a possibility as with all other observation studies. Not all relevant determinants of vaccine uptake, such as parental attitudes, language proficiency or local outreach efforts, can be accounted for using open access data aggregated data. Additionally, some covariates (eg, IMD and ethnicity) are available only as single point measures. Although area-level deprivation tends to remain stable over time,^46^ the use of fixed values may not fully capture recent demographic shifts. Nonetheless, these indicators remain important proxies for structural disadvantage, which is known to shape immunisation behaviour.

Second, the representativeness of variables from the national GP patients survey might be limited due to the low response rate of around 27%.^47^ Responses might reflect experiences of those who are already more engaged with healthcare services, while under-representing the populations that are less likely to participate. Still, these variables remain valuable for capturing the broader patterns of patient engagement across GPs.

Third, there is currently no centralised registry or reporting system in England that documents all vaccination equity improvement initiatives and the degree to which they are community-led. Our efforts to identify other similar vaccination initiatives through a brief audit might not comprehensively map every relevant intervention that may have been active during the study period. However, this is a broader challenge that affects all evaluations of localised public health interventions, particularly those of non-randomised design.

Finally, our decision to use GP level aggregated data might affect SCM matching due to the lack of granularity in covariate and outcome measurements. Without access to individual-level records, it is impossible to account for the within-practice variation. While a similar evaluation could be replicated using individual-level records, access to such data is often restricted. Thus, by testing the feasibility of using open access sources such as the COVER dataset, we aim to demonstrate a reproducible approach that can be adopted in local settings with limited access to line-listing data. In doing so, we also will inform the minimum data requirements for similar evaluations and provide reusable analytical code to support replication.

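### Neighbourhood (LSOA) uptake can only be apportioned from practice figures, so rerunning the permutation test on LSOAs would dilute the effect and make the p-value too small

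*Protocol article*

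**What the plan says.** The Vaccine uptake section describes COVER as quarterly statistics "for children aged 5 years and under at the general practice (GP) level in England". The Timeline section describes a study "with data acquisition limited to downloading and curating publicly released datasets". Under Limitations the article adds: "Without access to individual-level records, it is impossible to account for the within-practice variation".

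The Sensitivity analysis section nevertheless commits to a neighbourhood-level version: "we will rerun the evaluation using vaccine uptake aggregated to a small area neighbourhood level (LSOA"), on the ground that it is one "which may better reflect the community-based nature of the intervention". The Abstract is more cautious and lists "the feasibility of analysis at small area neighbourhood level" among the things to be examined.

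On size, the Covariates section notes that "LSOAs are small statistical areas representing neighbourhoods of ~ 1500 people". The practice-to-LSOA link that the article names is the count of registered patients per practice by LSOA (Covariates section and Table 2). Figure 2 already maps coverage for MSOAs, another small-area geography, and its caption says "Coverage data are based on GP-level uptake reported through the COVER programme".

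The Analysis section defines 19 intervention practices by whether the practice's population-weighted centroid lies within 1 km of a site. It describes one form of inference: 250 permutations that reassign treatment among control units.

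**The concern.** The change of unit suggests a finer view of the outcome, but the listed sources contain no finer outcome. A practice draws children from many LSOAs and an LSOA sends children to several practices, so an LSOA percentage has to be built from practice percentages. Two problems follow if the evaluation is simply repeated on those values.

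- **Blending.** LSOAs near a site carry some uptake from control practices, and donor LSOAs further out carry some from intervention practices. The contrast shrinks.
- **Dependence.** Neighbouring LSOAs share practices, so their values move together. Treated LSOAs are neighbours by design. Permuted sets of LSOAs drawn from the whole donor pool are scattered and share far fewer practices. Shuffling LSOA labels therefore gives a null distribution that is too narrow.

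What is at stake is how this check is read. With a diluted estimate and an over-narrow null, neither agreement nor disagreement with the practice-level result says much about robustness. The article also plans to publish its code for reuse in similar evaluations, so the construction could be copied.

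**Working it through.** The article gives no power, error rate or expected number of LSOAs for this analysis, so there is no stated figure to reproduce. The check is structural, followed by an illustration of size.

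**Inputs from the article:** outcome per practice and quarter (Vaccine uptake); public downloads only (Timeline); registrations by LSOA (Table 2); 19 intervention practices, the 1 km rule and 250 permutations (Analysis); anticipated effect 5 to 15 percentage points (Expected results).

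**Step 1, the outcome.** Let y_p be uptake at practice p and w_lp the share of LSOA l's children registered there. With these sources the LSOA value is z_l = Σ_p w_lp y_p. The article does not state this formula. It is inferred from the listed data.

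**Step 2, information.** The vector z is a linear map of y, so it cannot hold more independent values than there are practices. In the simulation below, 2700 or 4500 LSOAs gave a weight matrix of rank 900, the number of practices.

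**Step 3, dilution.** If uptake rises by δ at intervention practices, z_l rises by δ × s_l, where s_l is the share of that LSOA's children at intervention practices. The LSOA contrast is δ × (mean s in treated LSOAs − mean s in donor LSOAs), which is below δ whenever the two kinds of practice mix.

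**Step 4, dependence.** With independent practice changes of variance σ², Cov(z_l, z_m) = σ² Σ_p w_lp w_mp. This is positive for any two LSOAs that share a practice.

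**Step 5, rough size by formula.** Suppose the information of 19 practices is spread over n treated LSOAs counted as independent. The standard error is then understated by √(n/19), and the type I error is 2 × [1 − Φ(1.96/√(n/19))]. The values of n are assumed.
- n = 40: factor 1.45, type I error 18%
- n = 60: factor 1.78, type I error 27%
- n = 100: factor 2.29, type I error 39%

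**Step 6, rough size by simulation.** Assumptions: 900 practices in a 30 × 30 km area; 3 or 5 LSOAs per practice; each LSOA's children split over up to 8 nearby practices with a distance-decay scale of 0.3, 0.7 or 1.5 km; nine sites with 1 km buffers; independent practice changes under the null; 250 permutations; 300 replicates; two-sided 5%. The statistic was a plain treated-minus-control difference.

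| LSOAs per practice | Decay (km) | Treated practices | Treated LSOAs | Type I, practices permuted | Type I, LSOAs permuted | 5.0-point effect becomes |
|---|---|---|---|---|---|---|
| 3 | 0.3 | 21 | 62 | 6.3% | 40.3% | 3.45 |
| 3 | 0.7 | 21 | 62 | 3.7% | 46.3% | 2.77 |
| 3 | 1.5 | 22 | 65 | 3.7% | 43.7% | 2.28 |
| 5 | 0.3 | 21 | 107 | 3.7% | 50.7% | 3.38 |
| 5 | 0.7 | 22 | 113 | 7.0% | 51.0% | 2.79 |
| 5 | 1.5 | 22 | 108 | 6.0% | 54.0% | 2.21 |

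The simulation error around 5% is √(0.05 × 0.95/300) = 1.3 points, so the practice-level column is consistent with nominal. By Step 3, the shrinkage implies a difference in mean shares of 2.21/5.0 = 0.44 to 3.45/5.0 = 0.69. Between 97% and 98% of treated LSOAs drew on both kinds of practice, and 59 to 256 donor LSOAs had more than 5% of their children at treated practices.

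**The case against.** The strongest reply is that the article gives this analysis one sentence. It does not say how LSOA uptake is built, when an LSOA counts as exposed, or what is permuted. Such detail commonly sits in a fuller plan, and permuting by practice or by blocks of neighbouring areas would largely remove the significance problem. This stands in part: the p-value point is conditional. But the article says the evaluation will be rerun and describes only one inference, the shuffling of unit labels. The apportionment itself does not depend on unstated detail, because the listed sources leave no other route.

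A reader might go further and infer that the analysis adds nothing and that LSOA values are copies of one another. The documents do not support that. Two LSOAs served by the same practices differ whenever their registration shares differ, so the values are correlated mixes. Exposure could be defined by residence, and deprivation and ethnicity could be used at their native LSOA level. The claim of no new information holds for the outcome only.

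The sizes are also open to challenge. The formula assumes that only 19 practices contribute, although treated LSOAs also contain control practices' uptake. Applied to the simulation's own counts it gives about 25% (62 LSOAs, 21 practices) to 39% (113 LSOAs, 22 practices), against a simulated 40% to 54%. The simulation did not fit the calibration weights on 18 pre-intervention quarters or use an England-wide donor pool. Only the direction is established.

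Finally, the Abstract calls this a feasibility question, and Limitations already concedes that within-practice variation is out of reach. Both are true and lower the severity. Neither mentions the apportionment or its effect on the test.

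**Conclusion.** The point holds in conditional form and is of low severity. With the listed sources, LSOA uptake is apportioned practice uptake and brings no new outcome information. If LSOAs become the permuted units, the p-value will be too small and the estimate will be pulled towards zero. The direction was the same in all six simulated settings. The error rates and the degree of shrinkage depend on assumed geography and a simplified statistic, so they should not be quoted as the error rate of this study.

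A reader might infer that the trial's main finding is at risk. It is not: the Analysis section fixes general practices as the unit, and this sensitivity analysis does not feed into the primary estimate. The conclusion would change if an LSOA-level or individual-level uptake source were obtained, but the article names none.

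**What to change.** - State that LSOA uptake is apportioned from practice-level COVER data using registrations by LSOA, and give the rule by which an LSOA counts as exposed.
- Either report the LSOA results descriptively or, if they are tested, permute treatment at practice level, preferably in groups of neighbouring practices, and rebuild the LSOA mix in each permutation. This variant was not simulated. The case for it is that it permutes at the level where uptake is observed, as did the practice-level runs that held close to 5%.
- Exclude from the donor pool any LSOA with a material share of children registered at intervention practices, with the threshold set in advance.
- Do not present agreement with the practice-level result as independent corroboration.

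The cost is a few sentences and some extra code. Analysis starts only after the audit planned for January to April 2026. The downside is one fewer apparently independent robustness check.

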### Timeline

The study uses data from the COVER programme, with data acquisition limited to downloading and curating publicly released datasets. The audit form is planned for January to April 2026. Data analysis will begin following completion of the audit, and the study is expected to conclude by January 2027.

### Patient and public involvement

Although there were no patients or members of the public directly involved in the design of this evaluation, the intervention itself was co-produced with members of the public, as described in the intervention details section. Also, as part of the ReCITE project, a co-researcher training programme has been developed to support public involvement throughout the research process. This programme provides training in research methods for members of the public who have either participated in or been affected by the intervention. Trained co-researchers will contribute to the interpretation of results and the communication of findings to lay audiences.

### Ethics and dissemination

This study will be conducted as part of the ReCITE project, which has received ethical approval from the Liverpool School of Tropical Medicine Research Ethics Committee (Reference: 24–018). Findings will be shared with the project funder, submitted for publication in a peer-reviewed journal and communicated to the public through plain language summaries. The analytical code will be made publicly available through an online repository (GitHub), along with any processed data derived from open-access sources. This will enable full reproduction of the analysis and support methodological reuse in similar evaluations.

## Discussion

### Summary

This protocol outlines the design of a population-level evaluation of a community-led initiative aimed at increasing childhood vaccine uptake in Liverpool using publicly available GP-level data and SCM. While the primary outcomes are MMR1 and MMR2 uptake, the inclusion of other childhood vaccines, such as the 6-in-1, rotavirus and PCV booster, in the analysis allows for the assessment of broader shifts in routine immunisation behaviour, which may also be influenced by community engagement activities. This study also serves as a methodological pilot for evaluating similar hyper-localised community-led interventions targeting vaccination uptake in the UK, including interventions implemented under the ReCITE programme (Building Research by Communities to Address Inequities Through Expression),^41^ which tackles health inequities across the Cheshire and Merseyside region in the UK.

